**Fig. 5 Fig5:**
[figure not shown]
Schedule of enrollment, interventions and assessments. *PACU* Post Anesthesia Care Unit, *ASA* American Society of Anesthesiologists, *TWA* time-weighted average

#### Safety

All adverse and serious adverse events, irrespective of causality, will be collected and reviewed by the principal investigator and reported to the Medical Ethics Committee of the AMC Amsterdam. Adverse events are defined as any undesirable experience occurring to a subject during the study, whether or not considered related to the experimental intervention. All adverse events reported spontaneously by the subject or observed by the investigator or his staff will be recorded.

Serious adverse events are defined as any untoward medical occurrence or effect that: results in death; is life-threatening (at the time of the event); requires hospitalization or prolongation of existing inpatients’ hospitalization; results in persistent or significant disability or incapacity; is a congenital anomaly or birth defect; or any other important medical event that did not result in any of the outcomes listed above due to medical or surgical intervention but could have been based upon appropriate judgment by the investigator. An elective hospital admission will not be considered as a serious adverse event.

We cover the potential harm of overtreatment by assessing the cumulative treatment dose during surgery and by assessing the amount of hypertension (in TWA, AUC, incidence, total time and percentage of time spent in hypertension). We will compare the outcomes between the control and intervention groups.

Insurance is provided for all participating subjects by the AMC Amsterdam.

#### Sample size calculation (phase B)

Difference in primary outcome will be compared using the Student’s *t* test or the Mann-Whitney *U* test, based on normality. A statistician performed the sample-size analysis. Based on previously published blood pressure data during surgery, it was estimated that our control group would have a TWA of 0.50 and a difference of 0.38 or larger between two study groups would be clinically relevant [18]. An effect size of 0.74 was calculated by dividing the estimated difference of 0.38 (mean experimental group − mean control group) by the standard deviation of 0.51. A sample size of 30 in each group in the randomized phase will have 80% power to detect an effect size of 0.74 using a two-group *t* test with a 0.05 two-sided significance level. Sample size was calculated using R 2017 [19].

The baseline data collection enables us to calculate the normal TWA spent in hypotension in our hospital and will be used to verify our sample-size analysis.

Patients who are randomized but in whom no study measurement was started, no arterial line was placed or when technical failure of the HemoSphere device prevented data collection will be excluded and replaced.

### Statistical analyses

We will analyze the data based on an intention-to-treat principle. The intention-to-treat population is defined as all patients who meet the inclusion criteria at the end of the study period.

Continuous data will be presented as median with range and/or interquartile range (IQR), or mean with standard deviation and range when normally distributed. Normality of distribution will be assessed visually with histograms and Q-Q plots. Categorical data were given as frequencies with percentages. For each of the analyses a probability value of *p* < 0.05 will be considered statistically significant.

Our primary outcome is TWA in hypotension (phase B). We will compare the TWA of each arm using the Student’s *t* test or Mann-Whitney *U* test, depending on the distribution of the data. The baseline data collection enables us to calculate the normal TWA spent in hypotension in our hospital and will be used to verify the representativeness of our control group. We will compare the TWA in the baseline group (phase A) to the TWA in the control arm (phase B).

The secondary and exploratory research questions involving categorical data will be analyzed using the *χ*^2^ test/Fisher’s exact test and secondary research questions involving continuous (numerical) data will be analyzed using the Student’s *t* test or the Mann-Whitney *U* test. Feasibility of working with HPI will be analyzed using qualitative research methods, reporting the number of protocol violations with reasons. Underlying causes of intraoperative hypotension will be analyzed using our study flowchart (Fig. 2) on all 100 patients. To assess whether use of HPI intraoperatively results in less postoperative hypotension at the PACU the TWA in hypotension during PACU stay will be analyzed. The exploratory questions will not be addressed in the primary article. All analyses for the primary article will be done using Matlab (R2018b) and SPSS (version 25).

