**Methods/design:**

We aim to include 100 adult patients undergoing non-cardiac surgery with an anticipated duration of more than 2 h, necessitating the use of an arterial line, and an intraoperatively targeted mean arterial pressure (MAP) of > 65 mmHg. This study is divided into two parts; in phase A baseline TWA data from 40 patients will be collected prospectively. A device (HemoSphere) with HPI software will be connected but fully covered. Phase B is designed as a single-center, randomized controlled trial were 60 patients will be randomized with computer-generated blocks of four, six or eight, with an allocation ratio of 1:1. In the intervention arm the HemoSphere with HPI will be used to guide treatment; in the control arm the HemoSphere with HPI software will be connected but fully covered. The primary outcome is the TWA in hypotension during surgery.

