### Eligibility criteria

Adult patients (aged 18 years or older) scheduled to undergo an elective, clinical, non-cardiac, surgical procedure under general anesthesia and requiring an arterial line will be eligible for inclusion. A desired target MAP of 65 mmHg during surgery is used as an inclusion criterion, to ensure that both study arms will be similar in this aspect. Patients undergoing emergency surgery are not eligible. Patients with cardiac failure, severe cardiac shunts, severe aortic stenosis and severe cardiac arrhythmias will be excluded in accordance with the summary of product characteristics of the HPI algorithm. Patients enduring significant hypotension before surgery and patients requiring dialysis will be excluded. Patients planned to undergo liver surgery or vascular surgery will be excluded because of the use of vascular clamping. For this trial, anesthesiologists are not allowed to use a different hemodynamics treatment protocol besides our study protocol; therefore, an exclusion criterion is the planned usage of a perioperative Goal Directed Fluid Therapy (GDFT) protocol.

Researchers will screen all patients presenting for elective, non-cardiac, non-day-case surgery. Patients will be contacted and informed in case of eligibility. Patient informed consent will be obtained the day prior to surgery.

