### Study procedures and interventions

The HPI algorithm was previously internally and externally validated [15]. The HPI algorithm is only available on the HemoSphere and Flotrac monitoring systems and requires the use of a FlotracIQ sensor connected to an arterial line (Edwards Lifesciences Corp., Irvine, CA, USA). The FlotracIQ sensor has a splitter which enables the splitting of the arterial blood pressure signal to facilitate a blood pressure signal on both the Philips monitor (standard care) and the HemoSphere monitor (study).

In all study participants this system will be connected to both the HemoSphere and the Philips monitor. The Philips monitor displays the MAP, systole, diastole and the pulse pressure variation as per standard care protocol in our hospital. In the baseline group (phase A) and in the control arm (phase B) the HemoSphere with HPI software will be connected; however, the screen will be fully covered. In the control arm the anesthesiologist solely uses the variables visible on the Philips monitor to guide hemodynamic treatment. In the intervention arm the HemoSphere with HPI software will be visible and the perioperative hemodynamic management will be based on both the Philips monitor and the HemoSphere monitor. Use of the HPI software is additional to standard care, it is not used as a replacement of standard care. In the intervention arm we will ask the anesthesiologist and anesthesia nurse to use the study treatment flowchart (Fig. 2). If the HPI alarm goes off, which entails both a sound and a flickering light, we ask the anesthesiologist to act upon this alarm preferably within 2 min. Use of the study treatment flowchart ensures that the anesthesiologist has to think about the underlying cause. The HemoSphere with HPI software has a second screen (Fig. 3) with variables that provide information about the underlying cause of the predicted hypotension (http://ht.edwards.com/scin/edwards/eu/sitecollectionimages/edwards/eu%20hpi%20brochure_digitalversion_largerfile%20for%20online%20use_10-6.pdf).

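### The intention-to-treat population is defined by an eligibility check at the end of the study rather than by randomization and allocated arm, so the primary comparison is not fully protected by randomization

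*Protocol article*

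**What the plan says.** All references are to the protocol article.

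- **Statistical analyses** gives the principle: "We will analyze the data based on an intention-to-treat principle". The next sentence gives the population: "The intention-to-treat population is defined as all patients who meet the inclusion criteria at the end of the study period". The same section ties the primary outcome to phase B and compares the two arms.
- **Sample size calculation (phase B)** has a separate rule for some randomized patients. It begins "Patients who are randomized but in whom no study measurement was started, no arterial line was placed" and ends "technical failure of the HemoSphere device prevented data collection will be excluded and replaced".
- **Eligibility criteria** includes patients having elective non-cardiac surgery "under general anesthesia and requiring an arterial line will be eligible for inclusion", and adds: "A desired target MAP of 65 mmHg during surgery is used as an inclusion criterion". It sets no limit on duration of surgery.
- **Abstract, Methods/design** describes the patients as having surgery "with an anticipated duration of more than 2 h" and gives the target MAP as above 65 mmHg.
- **Study procedures and interventions** makes the treatment open to the team: "In the intervention arm the HemoSphere with HPI software will be visible". In the control arm the screen is covered.
- **Randomization and blinding** has an independent researcher, blinded to allocation, analyse the primary outcome. It does not say who decides eligibility for the analysis set.

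**The concern.** An intention-to-treat set is fixed by two facts: the patient was randomized, and the patient is analysed in the arm assigned. The definition here uses neither. It substitutes an eligibility judgement dated to the end of the study period, and no other section restores an all-randomized set.

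If a randomized patient with a recorded TWA can be dropped because eligibility is later judged not to have been met, the arms being compared are no longer simply those that randomization produced. The article does not confine that judgement to information available before allocation and does not require it to be made without knowledge of the arm. The result could carry the intention-to-treat label without meeting it.

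**Working it through.** **1. The plan's own figure.** Inputs from Sample size calculation (phase B): effect size 0.74, 30 per arm, two-sided 0.05, two-group t test. The noncentrality is 0.74 / √(1/30 + 1/30) = 2.87 on 58 degrees of freedom, which gives 80.5% power. Thirty is the smallest number per arm that reaches 80%, so the stated figure reproduces. Analysing all randomized patients changes none of these inputs.

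**2. The two exclusion routes side by side.**

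| | Sample size section | Statistical analyses section |
|---|---|---|
| Grounds | No measurement started, no arterial line, device failure | Inclusion criteria not met at the end of the study period |
| Link to missing TWA | Direct | None required |
| Replacement | Yes | Not stated |
| Blind to arm | Not stated | Not stated |
| Limited to pre-randomization data | No | Not stated |

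The first route is specific and largely concerns patients without outcome data. The second is open-ended and can remove patients who have a TWA.

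**3. Which criteria apply.** If membership turns on the inclusion criteria, their text matters. The Abstract has an anticipated duration above 2 h; Eligibility criteria has no duration limit. The target MAP is above 65 mmHg in one place and 65 mmHg in the other. A patient with a shorter planned operation would be in the set under one statement and out under the other.

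**4. Cost in power if removals are unrelated to arm and outcome.** The documents give no number of removals, so 1 to 5 without replacement is an assumption. With effect size 0.74:

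| Removed | From one arm | From each arm |
|---|---|---|
| 0 | 80.5% | 80.5% |
| 1 | 79.8% | 79.1% |
| 5 | 76.5% | 72.7% |

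In this case there is no bias, only a modest loss of power.

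**5. The other end of the range.** This is a deliberate worst case, and its assumptions are not in the documents. TWA is log-normal with mean 0.50 and SD 0.51 in both arms (log-scale variance ln(1 + (0.51/0.50)²) = 0.713), there is no true effect, and the highest-TWA patients are removed from the intervention arm only. Simulation used 20,000 data sets for the t test and 4,000 for Mann-Whitney.

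| Removed of 30 | Spurious difference | t test rejects | Mann-Whitney rejects |
|---|---|---|---|
| 0 | about 0 | 4.4% | 4.6% |
| 1 | 0.06 | 7.5% | 5.7% |
| 2 | 0.09 | 11.8% | 7.3% |
| 3 | 0.12 | 17.5% | 9.9% |

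Steps 4 and 5 bracket what the wording leaves open. They do not estimate what will happen.

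**The case against.** The strongest reply is that the sentence is loose but its context repairs most of it. The preceding sentence adopts intention-to-treat. The primary comparison is limited to the phase B arms, which patients enter only by randomization. Most criteria are worded as pre-operative intent (scheduled surgery, a desired target, an anticipated duration), so a change during surgery does not clearly alter whether they were met. The end of the study period may simply be the date on which the set is closed. The primary analyst is independent and blinded.

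Much of this stands, and it rules out several stronger readings that a reader might infer:

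- *The comparison loses its randomized basis, or phase A patients enter it.* The restriction to the phase B arms answers this. What remains is incomplete protection.
- *Patients are removed with outcomes known.* The article does not say so. It fails to prevent it, which is a narrower point.
- *The effect would be overstated by 11% or 25%.* Suppose 3 or 6 of 30 intervention patients had the control TWA of 0.50 instead of 0.12 (0.50 − 0.38). The all-randomized difference is then 0.50 − (0.9 × 0.12 + 0.1 × 0.50) = 0.342, or 0.50 − (0.8 × 0.12 + 0.2 × 0.50) = 0.304. Dropping those patients gives 0.38, and 0.38/0.342 = 1.11, 0.38/0.304 = 1.25. But nothing in the documents links failed eligibility to non-response or makes removal one-sided. If patients ineligible at baseline were removed alike from both arms, 0.38 would be a valid effect in eligible patients.

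The context does not supply the missing terms. No sentence says that all randomized patients are analysed, and a blinded analyst cannot repair a set that others have already selected. A statistical analysis plan that is not shown does not excuse a rule stated here; if it said otherwise, it would contradict the published definition.

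**Conclusion.** The concern holds in limited form. The stated population is not an intention-to-treat population and conflicts with the principle announced just before it. It permits an eligibility filter after randomization without requiring that eligibility be judged blind to arm or on pre-randomization data. With an unblinded treating team, this leaves the primary comparison not fully protected by randomization.

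The size and direction of any bias cannot be derived from the documents. It may be nil if removals are unrelated to arm and outcome. The worst-case figures show only that, at 30 per arm (1/30 = 3.3% of an arm per patient), a few selective removals could matter. The conclusion rests on the definition itself, not on those figures. The mismatch in inclusion criteria is a separate inconsistency; it does not show bias, but it makes membership of the set ambiguous.

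**What to change.** Replace the definition with wording such as: *The intention-to-treat population is all patients randomized in phase B, analysed in the arm to which they were allocated, regardless of any later judgement about eligibility.*

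That sentence alone would collide with the exclude-and-replace rule in Sample size calculation (phase B), so also:

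1. Report, by arm and reason, every randomized patient excluded or replaced for no measurement, no arterial line or device failure.
2. State how randomized patients without TWA data are handled. If they are left out, call the primary set modified intention-to-treat.
3. Allow no other exclusion after randomization.
4. Report eligibility violations by arm, and make any eligibility-based set a sensitivity analysis.
5. Reconcile the Abstract and Eligibility criteria on anticipated duration and on the wording of the target MAP.

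The cost is a few sentences and a fuller participant flow report. The planned 30 per arm and its 80.5% power are unchanged. The downside is that the estimated effect may be slightly smaller, because patients who would have been filtered out stay in.

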### Study outline

Patients will be contacted on the surgical ward or at the pre-operative assessment clinic, and written information and oral explanation will be provided. Patient characteristics, medical history, medication use and American Society of Anesthesiologists (ASA) physical score classification will be collected from the medical records. Blood pressure measured at the outpatient clinic, blood pressure measured the day before surgery on the ward and blood pressure measured in the operating theater before induction will also be registered.

Phase A: TWA and normal treatment behavior of anesthesiologists in the AMC will be collected prospectively as baseline data. These data will be used to verify our sample size calculation for phase B and to study whether our control group is representative for the study population by comparing the baseline group versus the control group. During this phase of the study the treating anesthesiologist and anesthesia nurse will not be informed about the aim of the study or the endpoints measured.

Phase B: in this phase, patients will be randomized. The treating anesthesiologist and the anesthesia nurse will be informed about the study protocol and the usage of the HPI algorithm (with the secondary screen) the day before the surgery. All study interventions are to be performed by trained study personnel or the treating anesthesiologist, following instructions from the researchers.

In both study phases a researcher will be present – continuously – during all surgeries to note surgical and anesthetic details.

For a Consolidated Standards of Reporting Trials (CONSORT) flow diagram of the study see Fig. 1. All data will be entered using an electronic Clinical Report Form build in Castor EDC, a Good-Clinical-Practice-compliant data management system [17].

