### Randomization and blinding

In phase B, patients will be randomized to either use of the HPI algorithm intraoperatively (intervention arm) or standard care (control arm). We will use a computer-generated, permutated block randomization, with a 1:1 allocation ratio. This will result in concealed and varying permutated block sizes of four, six or eight patients.

Randomization will be performed by a designated researcher. An independent researcher (not involved in collecting study data), blinded for the randomization, will perform the statistical analysis for the primary outcome.

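### The primary TWA comparison makes no use of the registered pre-induction blood pressure: a valid test, but possible precision and prespecified protection against chance imbalance are given up

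*Protocol article*

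**What the plan says.** - **Primary analysis (Statistical analyses):** the sentence that fixes the test begins "We will compare the TWA of each arm using the" and goes on to name two unadjusted options, the t test and the Mann-Whitney test, with the choice resting on how the data are distributed. The sample size section names the same pair of tests. Neither place mentions a covariate.
- **Baseline data (Study outline):** besides a clinic reading and a ward reading from the day before surgery, "blood pressure measured in the operating theater before induction will also be registered".
- **Randomization (Randomization and blinding):** "We will use a computer-generated, permutated block randomization, with a 1:1 allocation ratio". Block sizes are four, six or eight. No stratification factor is named.
- **Sample size:** "A sample size of 30 in each group in the randomized phase will have 80% power to detect an effect size of 0.74". The calculation is for an unadjusted t test at a two-sided alpha of 0.05. The inputs are a control TWA of 0.50, a difference of 0.38 and an SD of 0.51.

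The article gives pre-operative pressure no role in the primary comparison and does not report its correlation with TWA.

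**The concern.** TWA measures how far and how long MAP lies below 65 mmHg. The patient's own pressure just before anesthesia is a natural candidate to predict it. It is measured before the intraoperative intervention starts, so adjusting for it is legitimate.

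Two things are at stake:

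- **Precision.** If baseline pressure is prognostic, adjustment removes part of the residual variance from a trial with only 30 patients per arm.
- **Chance imbalance.** With no stratification factor named, baseline balance rests on chance. If a visible gap in baseline pressure appears and no adjustment was fixed beforehand, any later adjustment is post hoc and open to challenge. This can only be settled before the data are seen.

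**Working it through.** **Inputs from the article:** n = 30 per arm; two-sided alpha 0.05; difference 0.38; SD 0.51; stated effect size 0.74 (0.38/0.51 = 0.745).

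**Assumption:** r, the correlation of pre-induction pressure with TWA, is not given. It is varied from 0 to 0.5; only its absolute size matters here.

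**Step 1, the stated power.** Noncentral t with 58 degrees of freedom and noncentrality 0.74 × √(30/2) = 2.87 gives 80.5%. The stated 80% reproduces.

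**Step 2, power after adjustment.** The residual SD becomes 0.51 × √(1 − r²). One degree of freedom is lost (57 remain), and estimating the slope inflates the variance by about 1 + 1/56. The effective effect size is therefore 0.74 / [√(1 − r²) × √(57/56)].

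| Assumed r | Variance removed (r²) | Power at 30 per arm | 95% CI half-width |
|---|---|---|---|
| unadjusted | – | 80.5% | 0.264 |
| 0 | 0% | 79.7% | 0.266 |
| 0.2 | 4% | 81.3% | 0.261 |
| 0.3 | 9% | 83.3% | 0.254 |
| 0.4 | 16% | 86.1% | 0.244 |
| 0.5 | 25% | 89.7% | 0.230 |

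Break-even: the gain offsets the slope cost when 1 − r² = 56/57, so r² = 1/57 and |r| is about 0.13.

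**Step 3, chance imbalance.** The between-arm difference in a baseline variable has a standard error of √(2/30) = 0.258 SD. A gap larger than 0.5 SD is 0.5/0.258 = 1.94 standard errors, which has a two-sided probability of about 5%. A gap of that size shifts the unadjusted TWA difference by r × 0.51 × 0.5:

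- r = 0.3: 0.076, or 20% of 0.38
- r = 0.5: 0.128, or 34% of 0.38

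For scale, the standard error of the unadjusted TWA difference is 0.51 × 0.258 = 0.13.

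**Step 4, does the gain survive skew?** TWA cannot be negative, yet 0.50 − 0.51 is below zero, so the planning figures imply right skew. The figures in step 2 are normal-theory figures. Quade's rank analysis of covariance was therefore simulated against Mann-Whitney (gamma-distributed TWA with mean 0.50 and SD 0.51, 30 per arm, 4,000 runs, illustrative treatment ratio 0.45). Quade's type I error was 4.9% to 5.5%. Its power against Mann-Whitney was 71% v 71% at latent r = 0, 75% v 71% at 0.3 and 82% v 72% at 0.5. With excess zeros added, type I error stayed near 5% and the gain was roughly 4 to 8 points at latent r of 0.3 to 0.5. These powers depend on the assumed distribution and treatment ratio; only the contrast between the two tests matters here.

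**The case against.** The strongest reply is that nothing here is wrong. An unadjusted two-group test in a 1:1 randomized trial keeps its type I error, is unbiased over randomization, and is the test for which the trial was sized. That stands in full. A reader might infer that the primary analysis is biased, invalid or underpowered; the article does not support any of these.

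A second reply is that covariates and sensitivity models belong in the statistical analysis plan, which the article says is available on request but which is not shown here. This stands in part. The plan may contain an adjusted analysis, and an article that names no stratification factor does not prove that there was none. But the article itself names the primary test twice and fixes it as unadjusted, so this is a stated choice and not a detail left open.

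A third reply is that the benefit rests on an unknown correlation. This also stands. Below |r| of about 0.13 adjustment gains nothing, and at 0.2 the gain is under 1 point. The eligibility criteria may also weaken the link: they exclude significant hypotension before surgery, which narrows the covariate, and they set a common MAP target toward which patients are treated.

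Two further limits apply. Adjustment handles only the modelled part of one covariate, so it would be too much to say that it removes the effect of chance imbalance. And a rank-test p-value can disagree with a mean difference from a linear model, because the two target different quantities; each needs a defined role.

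**Conclusion.** The point holds as a missed opportunity, not as an error. The stated test and its 80% power are sound on the article's own inputs. Depending on the assumed correlation, adjustment changes power by somewhere between −0.8 points (r = 0) and about +9 points (r = 0.5), and by about +3 points at r = 0.3. The trade is lopsided: the worst case is small and the best case is useful.

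The imbalance argument does not rest on the size of the power gain, but it too needs a prognostic covariate. In roughly one such trial in twenty, a gap of more than 0.5 SD would move the estimate by a fifth (r = 0.3) to a third (r = 0.5) of the target difference or more, with no agreed way to account for it.

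The figures assume a common SD of 0.51 and a roughly linear relation. The simulations suggest that the pattern carries over to a rank analysis of skewed TWA. That pre-induction pressure is complete for every patient is also not established: the article says that it is registered, not that no value will be missing.

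**What to change.** Before phase B is analysed, write into the plan:

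1. **Covariate:** pre-induction MAP, derived from the registered blood pressure, as the only covariate. If it is missing, use the ward value.
2. **Primary test:** Quade rank analysis of covariance, two-sided 0.05. State that this test alone decides significance.
3. **Estimate:** the adjusted mean difference in TWA from a linear model with robust (HC3) standard errors, labelled descriptive.
4. **Sensitivity analysis:** the unadjusted comparison now planned.

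The 40 phase A patients have both variables under the protocol and can be used to check the correlation beforehand. The check will be rough: on the Fisher scale the standard error is 1/√(40 − 3) = 0.16, so an observed r of 0.3 is compatible with values from about 0 to 0.56. It should inform expectations and not serve as a strict gate.

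Cost: wording only, since the protocol already registers the data. The downsides are one degree of freedom, under 1 point of power if the covariate is not prognostic, and a slightly less simple test. If the sponsor prefers to keep the unadjusted test as primary, naming the adjusted analysis as a prespecified sensitivity analysis would still cover the imbalance concern.

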## Methods/design

### Study design

This investigator-initiated trial is divided into two phases. Phase A consists of prospective data collection in 40 patients to gain insight into the normal TWA in our study population. Phase-A data are collected to check our sample size for phase B and to verify if the control group is a representative sample. Phase B is a single-center, randomized controlled (1:1), superiority trial including 60 patients. The study takes place in the Academic Medical Center (AMC) Amsterdam, The Netherlands, a tertiary academic center. The study started with inclusion of the first patient in November 2017, the planned duration of the trial is 18 months. This trial has been registered with the NIH, U.S. National Library of Medicine at ClinicalTrials.gov (NCT03376347). This manuscript was written in accordance with the Standard Protocol Items: Recommendations for Interventional Trials (SPIRIT) guideline (Additional file 1) on reporting of intervention trial protocols [16].

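### Comparing 40 phase A patients with 30 controls, with no margin stated, cannot verify that the control arm is representative; report an estimate with its confidence interval instead

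*Protocol article*

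**What the plan says.** The protocol article gives phase A two jobs: checking the sample size of phase B and checking the control arm. Study design and Study outline both state the second job, and Statistical analyses repeats it: the baseline data "will be used to verify the representativeness of our control group". The method follows in one sentence: "We will compare the TWA in the baseline group (phase A) to the TWA in the control arm (phase B).

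The group sizes are fixed elsewhere. Study design says "Phase A consists of prospective data collection in 40 patients", and the sample size section gives "A sample size of 30 in each group in the randomized phase".

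No section states a margin, an acceptance limit or what follows from a mismatch. The comparison sentence names no test. The same section does set p < 0.05 as the significance threshold for every analysis, and the sentence sits in the paragraph that assigns the t test or Mann-Whitney test to the primary outcome.

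Staff awareness differs between the phases. In phase A, "the treating anesthesiologist and anesthesia nurse will not be informed about the aim of the study or the endpoints measured" (Study outline). In phase B the same section has the treating team informed about the protocol and the use of HPI on the day before surgery.

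**The concern.** To verify representativeness is to show similarity. A comparison designed to find differences does not do that unless it is precise enough to exclude differences that matter, and the reader must know which those are. Neither condition is met here. If the comparison gives p >= 0.05, the natural report is that the control arm was confirmed as representative, and the HPI effect would be read as an effect against usual care in this hospital. That reading could be wrong if briefed control teams managed blood pressure more closely than usual.

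The reverse error is also possible. A significant difference could arise by chance, from a different mix of operations or from the later period, and would be hard to attribute to an unrepresentative control arm.

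**Working it through.** **Inputs.** Phase A n = 40 and control n = 30 (Study design; Sample size calculation). Expected control TWA 0.50, clinically relevant difference 0.38, SD 0.51, two-sided alpha 0.05 (Sample size calculation). The 0.38 is stated for the two study groups, not for phase A against control.

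**1. The plan's own figure.** Effect size = 0.38/0.51 = 0.745, given as 0.74. A two-sample t test with 30 per group has power 80.5% at 0.74 (noncentral t). The stated 80% reproduces and is not in question.

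**2. Precision of phase A against control.**
- SE = 0.51 × √(1/40 + 1/30) = 0.123.
- 95% half-width = t(0.975; 68 df) × SE = 1.995 × 0.123 = 0.246, or 49% of 0.50.
- If the observed difference were exactly zero, shifts up to about 0.25 either way would remain compatible with the data. If it were just short of significance, the interval would reach about 0.246 + 0.246 = 0.49.

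**3. Chance that a t test at 0.05 misses a true shift** (40 vs 30, noncentral t):

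| True shift | Share of 0.50 | Not significant |
|---|---|---|
| 0.10 | 20% | 87% |
| 0.15 | 30% | 78% |
| 0.19 | 38% | 67% |
| 0.25 | 50% | 48% |
| 0.35 | 70% | 20% |
| 0.38 | 76% | 14% |

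The miss rate crosses 50% at a shift of 0.245.

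**4. Skewed TWA.** With mean 0.50 and SD 0.51 a right-skewed distribution is likely, and the protocol allows the Mann-Whitney test. Gamma and lognormal shapes with that mean and SD are my assumptions, with the control arm reduced proportionally. Simulated miss rates:

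| Shape | Test | 30% reduction | 50% reduction |
|---|---|---|---|
| Gamma | t | 74% | 26% |
| Gamma | Mann-Whitney | 77% | 34% |
| Lognormal | t | 71% | 21% |
| Lognormal | Mann-Whitney | 61% | 9–10% |

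Allowing for spread between simulation runs, the ranges are about 61–79% and 9–34%.

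**5. Could equivalence be claimed?** Two one-sided tests at 5% each, normal data, SD 0.51, no true difference: power is 84% for a margin of 0.38, 29% for 0.25 and about 1% for 0.19. The 90% half-width is 1.668 × 0.123 = 0.205, already wider than 0.19. For 80% power, about 71 per group are needed at 0.25 and 124 at 0.19. Only 0.38 comes from the document; the other margins are assumptions.

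**6. Why a shift below 0.38 can matter.** The planned intervention mean is 0.50 − 0.38 = 0.12. If the control mean were 0.31 (a shift of 0.19) and the intervention mean stayed at 0.12, the remaining difference would be 0.19. At SD 0.51, phase B power would fall from 81% to about 29%. By step 3, the phase A comparison would miss that shift in about two thirds of trials.

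**7. What the contrast measures.** The groups are not randomized to each other. They come from separate phases, and their clinical teams were told different things. The difference is the sum of sampling, period and awareness effects, which could also cancel.

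**The case against.** The strongest reply is that the protocol never says a non-significant result means representative. It says only that TWA will be compared; it names no test for that comparison and also commits to descriptive summaries. This stands in part: the significance test is inferred from the p < 0.05 rule and the neighbouring sentences. But the stated purpose is verification, and step 2 shows that the data cannot supply it at any margin clearly below 0.38, whatever test is used.

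A reader might infer that the check would pass most control arms that differ materially from usual care. The documents do not support that. They define no material shift for this comparison, and at the only difference they call clinically relevant, 0.38, a t test misses 14%. Misses are the majority only below about 0.245 with a t test, and below a smaller shift (between 0.15 and 0.19) with lognormal data and Mann-Whitney.

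A reader might also infer carry-over from control teams that treat intervention patients as well. That is plausible in one hospital, but no section says it. The documents support only that phase B teams are briefed.

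Keeping phase A staff unaware is a sensible way to record usual behaviour, and a shift caused by awareness is relevant to representativeness. The contrast is therefore worth reporting, although it cannot separate the causes.

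Finally, the primary comparison is randomized and uses phase B only. The phase A comparison does not enter it. That limits the severity of the point but does not rescue the claim of verification.

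**Conclusion.** The concern holds in a limited form. The protocol promises to verify representativeness with a comparison that has no margin and a 95% half-width of about 0.25, half the expected TWA. A non-significant result would leave shifts of 30% to 50% of usual TWA open, and a significant one could not be attributed to a single cause.

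The figures rest on the planning SD of 0.51, which phase A itself may revise; a smaller SD would narrow the interval. The skewed-data rates rest on assumed shapes. Reading the comparison as a significance test is an inference, but the precision argument does not depend on it.

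The point is minor to moderate. It concerns what may be said about the control arm, not the validity of the randomized comparison or its sample size.

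**What to change.** In Statistical analyses, replace the claim of verification with estimation, and align the matching sentences in Study design and Study outline:

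- Report control minus phase A TWA with a 95% confidence interval, beside the patient and surgery mix of both groups.
- State that p >= 0.05 will not be read as representativeness.
- Describe the result as a combined sampling, period and awareness difference.
- Make no equivalence claim unless the interval lies inside a margin stated and justified beforehand. At SD 0.51, a margin of 0.19 is out of reach with these numbers.

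This costs a rewording of a few sentences. It needs no new patients or data and leaves the primary analysis as it is. The trial gives up only a claim of verification that 40 and 30 patients cannot support.
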